## Background

1.

A core outcome set (COS) is an agreed standardized set of outcomes that should be measured and reported, as a minimum, in all clinical trials in specific areas of health or health care.
^
1
^ The concept of COS was introduced in China in 2013.
^
2
^ Chinese researchers have registered more than 80 COS for research in the Core Outcome Measures in Effectiveness Trials (COMET) database by 2022.

A search of the COMET database shows that more than 500 completed COS studies have been published by 2021. The number of COS varies by disease category. The top five disease categories are cancer, rheumatology, neurology, heart and circulation, orthopaedics and trauma.
^
3
^ However, the number of candidates vary by disease category. In addition, there are more than one COS for some conditions, while no COS exists in some other important conditions. Whether there are gaps between COS research and the burden of disease in China remains unclear.

There are some benefits to using COS in clinical trials, which include improving the consistency of outcome reporting, increasing the relevance of outcomes measured to decision-makers, and helping to identify potential selective outcome reporting bias. However, previous research has shown that COS uptake is low in most research areas.
^
4
^
^,^
^
5
^ Research shows that clinical trialists’ awareness and understanding of COS may facilitate the use of COS.
^
6
^ However, Chinese clinical trialists’ awareness, understanding and using of COS are unknown.

The aims of this study are to examine: (1) whether the top 25 diseases with the highest burden in China have relevant COS; (2) the use of COS in clinical trials registered in the Chinese Clinical Trial Registry for these 25 diseases; and (3) views of these clinical trialists on the knowledge, perceptions, and use of COS in relation to choosing outcomes, as well as barriers and facilitators to uptake of COS.

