**Inclusion criteria for clinical trials:**
(1)Randomised and non-randomised clinical trials;(2)The objectives of clinical trials are for disease therapy;(3)The prospective registration time should be in 2021 and 2022.

**Exclusion criteria for clinical trials:** The clinical trials are to assess the mechanisms of effect of interventions.

If the disease name in the COS is broader, we will further search subtypes of disease. RQ and XF will discuss the list of subtypes of disease, any disagreement will be discussed with a third investigator (HS). XF, WW, ZC, and SL will search for clinical trials from the Chinese Clinical Trial Registry and apply the inclusion and exclusion criteria to identify the eligible clinical trials. RQ will check the results.

**
*2.2.3 Comparison of COS with clinical trials*
**

Inclusion criteria:
(1)An eligible COS exists published since 2012.(2)The number of clinical trials with matching scope to an eligible COS is not less than 40.

A COS published since 2012 would be preferred to one published before 2012 for the analysis of COS uptake if one meets the eligibility criteria. A COS developed by Chinese researchers may be significant for Chinese clinical trialists. If there is an eligible COS developed by Chinese researchers, it will be included. If it does not meet the inclusion criteria for comparison of COS with clinical trials, then the prospective registration time for clinical trials will be expanded.

An online survey will be sent to trialists who registered clinical trials which are relevant to a specific COS. We anticipate a 50% non-response rate, thus if the number of trials is too small, it will be difficult to obtain a reasonable spread of perspectives from trialists about the use of the relevant COS. It was felt that responses from 20 trialists would be helpful based on a typical number of participants involved in qualitative research, thus requiring an anticipated 40 registered trials.

**
*2.2.4 Data extraction and analysis*
**

Data extraction for COS will include: author, title, publication time, condition, population, intervention, outcomes, and outcome measurement instruments (if applicable).

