**2.3.1.1 The process of online survey**

A survey will be sent to clinical trialists who have registered or completed a clinical trial that has overlapped scope between the trial and COS. We will identify the primary investigator’s name, email, and telephone number when we extract eligible clinical trials from the Chinese Clinical Trial Registry. We will send a Chinese translation of the COS deemed relevant to the trialists’ trials with questionnaire. When the primary investigators cannot be contacted via emails, the applicants for registration will be approached. We will examine trialists’ knowledge and awareness of COS. An online survey will be sent to clinical trialists, with one of three versions of the survey: 1) clinical trialists who report a full COS in their clinical trials; 2) clinical trialists who report only a few of outcomes in the COS; and 3) clinical trialists who do not report any outcome in the COS.

The survey will include both closed and open-ended questions. General information, such as gender, age, participants’ role (clinicians or researcher), specialty (traditional Chinese medicine, integrative medicine, or Western medicine), work experience, geographical area, professional qualification, and educational background will be collected. We will refer to the facilitators and barriers identified in previous research, including using of COS and clinical practice guidelines,
^
10
^
^,^
^
11
^ to develop open and closed questions to ask all participants. MK, PW, and RQ will discuss the questions in the questionnaires. The survey and other tools will be distributed into Chinese. RQ will translate tools into Chinese and the translation will then be sent to several researchers who have experience in COS research from a Chinese authors’ team and we will ask them to give comments. RQ, SL, ZC, and WW will discuss and determine the translation before distribution.

The structured questions in the survey are shown in extended data.

At the end of each survey, we will ask the trialists if they would like to attend a semi-structured interview.

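### The 40-trial floor is set by survey needs but gates the registry-based uptake comparison, and it is relaxed only for core outcome sets developed by Chinese researchers

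*Protocol article*

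**What the plan says.** Aim 2, in the Background of the protocol article, is to examine "the use of COS in clinical trials registered in the Chinese Clinical Trial Registry for these 25 diseases".

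Section 2.2.3 sets two conditions for comparing a COS with trials: publication since 2012, and "The number of clinical trials with matching scope to an eligible COS is not less than 40". The trials come from a two-year window (section 2.2.2): "The prospective registration time should be in 2021 and 2022".

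The reason for 40 follows in section 2.2.3 and concerns the survey alone. It begins "We anticipate a 50% non-response rate, thus if the number of trials is too small" and says that a reasonable spread of views would then be hard to obtain. It continues "It was felt that responses from 20 trialists would be helpful based on a typical number of participants involved in qualitative research", and ends "thus requiring an anticipated 40 registered trials".

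The same section makes one exception. An eligible COS developed by Chinese researchers is to be included, and "If it does not meet the inclusion criteria for comparison of COS with clinical trials, then the prospective registration time for clinical trials will be" widened. No such provision is stated for any other COS.

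Section 2.2.4 describes the comparison itself. For each trial, outcomes are classed as specific, general or non-matches to the COS and the percentages are summarised by medians. For each disease, the overlap in outcomes is given as a proportion. Section 2.1.3 adds that the study will explore whether uptake depends on development by Chinese researchers.

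The survey goes to people (section 2.3.1.1): "A survey will be sent to clinical trialists who have registered or completed a clinical trial that has overlapped scope between the trial and COS".

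**The concern.** A threshold derived for one component decides what enters another. The number of people who answer a questionnaire has no bearing on whether outcomes in a registry entry match a COS, and the article offers no separate reason for 40 in the comparison.

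Two results are at stake. First, the uptake figures would come only from COS with many matching trials, while the aims and the Discussion present them as describing the highest-burden diseases. Because the floor counts trials of matching scope, a narrow COS in a busy field can drop out as well as any COS in a quiet field. Second, since the window is widened only for Chinese-developed COS, the comparison by origin would set groups selected under different rules against each other.

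There is also a mismatch of units inside the survey argument. The target is a number of trialists and the floor is a number of trials.

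**Working it through.** **1. The plan's own figure.** Inputs from section 2.2.3: target 20 responses, non-response 50%. Trials needed = 20 / (1 − 0.5) = 40. The figure reproduces as an expected value, with one invitee per trial.

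**2. What the gated analysis needs.** The summaries in section 2.2.4 take two inputs: the outcomes listed in the COS and those listed in the registry entries. Neither the response rate nor the target of 20 enters. The derivation in step 1 therefore supports a floor for the survey and none for the comparison.

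**3. The rule applied to boundary cases**, each COS being otherwise eligible and published since 2012:

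| COS developed by | Matching trials, 2021-2022 | Result under section 2.2.3 |
|---|---|---|
| Others | 40 | compared, 2021-2022 trials |
| Others | 39 | not compared |
| Chinese researchers | 40 | compared, 2021-2022 trials |
| Chinese researchers | 39 | kept, wider registration window |

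The non-Chinese group then holds only COS with at least 40 trials from two registration years. The Chinese group can also hold COS with fewer trials in those years, topped up from other years. A difference in uptake between the groups could reflect origin, trial volume or registration period, and the design could not separate them.

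**4. Trials against people.** The number of distinct trialists behind 40 trials is at most 40, and lower if any investigator has registered more than one matching trial. Taking the best case of 40 distinct trialists who respond independently with probability 0.5:

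- Mean = 40 × 0.5 = 20; SD = √(40 × 0.5 × 0.5) = 3.16.
- 2.5th to 97.5th percentiles: 14 to 26 responses.
- P(at least 20) = 0.563.

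Sensitivity (the numbers of people and the response rates other than 50% are assumptions):

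| Distinct trialists | Response rate | Expected responses | P(at least 20) |
|---|---|---|---|
| 30 | 50% | 15 | 0.049 |
| 36 | 50% | 18 | 0.309 |
| 40 | 50% | 20 | 0.563 |
| 45 | 50% | 22.5 | 0.814 |
| 50 | 50% | 25 | 0.941 |
| 60 | 50% | 30 | 0.997 |
| 40 | 40% | 16 | 0.130 |
| 40 | 60% | 24 | 0.926 |

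**5. What cannot be computed.** The article gives no count of matching trials for any disease or COS, so the number falling below 40 is unknown.

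**The case against.** The strongest defence is that the components are linked. Section 2.3.1.1 assigns one of three survey versions according to whether a trial reports all, some or none of the COS, so the comparison feeds the survey, and one set of COS for both is a practical choice. That explains why every surveyed COS must be compared. It does not explain why every compared COS must be large enough to survey.

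It can also be said that aim 2 was never reachable for all 25 diseases, because the registry search is limited to diseases with a published COS. That stands. The relevant loss is among diseases that do have an eligible COS.

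Four stronger readings are tempting, and the article does not support them:

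- *Every COS below 40 trials is dropped.* Chinese-developed COS are kept by the wider window.
- *The survey reaches its target only about half the time.* The 56% belongs to a COS with exactly 40 distinct trialists and 50% response. Forty is a minimum, and the chance is 94% at 50 trialists.
- *Forty is an arithmetic error.* Twenty replies is described as helpful, by reference to typical qualitative samples, with no stated assurance. Forty distinct invitees meet that in expectation, and 14 to 19 replies would not be a failure on the plan's own terms.
- *Aim 2 is known to lose diseases.* Without trial counts, the loss could be none.

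Nor should the floor be attacked or defended with confidence-interval widths for a simple proportion of trials. The planned summaries are medians of per-trial percentages and outcome overlap per disease, which such widths do not describe.

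**Conclusion.** The point holds in this form: the survey rationale does not justify restricting the uptake comparison, and the one-sided exception unbalances the look at uptake by COS origin. It rests on reading the widening sentence in section 2.2.3 as referring to the Chinese-developed COS named just before it, which is the natural reading.

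The direction of selection is clear, towards higher-volume trial areas. Its size is not: the number of COS or diseases affected cannot be determined from the documents.

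The unit mismatch is secondary. At the floor, 40 trials yield at most 40 invitees and an expected 20 replies at best. The 14-to-26 range assumes 40 distinct trialists, independent replies and the protocol's 50% response.

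This is an inexpensive improvement that should be made, not a defect that undermines the study.

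**What to change.** - In section 2.2.3, remove criterion (2) from the uptake comparison. Report uptake for every eligible published COS that has in-scope trials, state the number of trials for each, and mark those resting on few trials as imprecise.
- Use the 2021-2022 window for all COS in the comparison by origin. If a wider window is still wanted for a Chinese-developed COS, report that result separately.
- Keep the floor only for choosing which COS go to the survey, and define it as distinct contactable investigators instead of registered trials. Describe 20 replies as the expected number at the floor, with a range of about 14 to 26 at 50% response.

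Cost: a wording change and outcome extraction for at most 39 further trials per added COS. Those trials must already be identified and matched for scope in order to apply the floor. COS below the floor would not be surveyed, so no further Chinese translations are needed. The price in interpretation is that some added estimates will rest on few trials, which the reported counts make visible.

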Sense organ diseases	Blindness and vision loss	Glaucoma, cataract, age-related macular degeneration, refraction disorders, near vision loss, other vision loss
Muscle disease	Osteoarthritis	/
Mental disorders	Anxiety disorders	/

**
*2.1.2 Identification of relevant COS*
**

We will manually search the COMET database and identify all COS for diseases/subtypes in the diseases list. We will identify if there are ongoing or completed relevant COS research. The study began on April 7
^th^, 2023 and is ongoing.

**
*2.1.3 Inclusion criteria for COS*
**

(1)The scope appears relevant to a disease in the diseases list;(2)COS for research should have included patient participants;

RQ will identify COS from the COMET database, and XF will check the results. Any discrepancies will be resolved by consensus discussion or by consulting a third reviewer (PW). RQ and PW will discuss all the COS for the 25 causes of DALY and determine which COS are eligible. The criterion related to the inclusion of patient participants follows previous work examining uptake of specific COS, and reflects the impact of patient participation on the choice of core outcomes.
^
8
^

The aim of COS is to promote a single unified approach to evaluating outcomes in a given condition throughout the world, however only 30% of COS published up to the end of 2021 have included participants from anywhere in Asia,
^
8
^ and the majority of COS developed in China are focused on traditional Chinese medicine (TCM). To explore whether the uptake of COS is influenced by whether it was developed by Chinese researchers, we will additionally include a COS published in a Chinese language journal if one meets the inclusion criteria above.

**
*2.1.4 Data extraction*
**

We will describe the number of ongoing and published COS for the highest burden of disease in China. Full texts will be retrieved for published COS only.

Previous COMET systematic reviews, and ongoing inclusion of published COS by COMET, will be used for details of published COS relevant to this work. Data extraction will include the intended use of recommendations, disease category, disease name, population characteristics (age, sex), interventions, geographical locations of COS developers, geographical locations of COS participants will be extracted, and whether patients participated.

**
*2.1.5 Data analysis*
**

Descriptive analysis will be used for general characteristics of COS.

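### Only COS developed by Chinese researchers get an open-ended wider trial-registration window, so whenever it is used the exploratory contrast by developer origin is mixed with registration period

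*Protocol article*

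**What the plan says.** All references are to the protocol article.

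- **Purpose (section 2.1.3).** The origin question is stated as "To explore whether the uptake of COS is influenced by whether it was developed by Chinese researchers". To serve it, the authors write "we will additionally include a COS published in a Chinese language journal", provided it meets the same inclusion criteria. Section 2.1.4 extracts the geographical location of COS developers.
- **Trial window (section 2.2.2).** "The prospective registration time should be in 2021 and 2022".
- **Entry to the uptake comparison (section 2.2.3).** Two criteria apply: "An eligible COS exists published since 2012" and "The number of clinical trials with matching scope to an eligible COS is not less than 40".
- **Exception (section 2.2.3).** "If there is an eligible COS developed by Chinese researchers, it will be included". Where such a COS fails the criteria, "then the prospective registration time for clinical trials will be expanded". No direction, length or stopping point is given, and no equivalent is offered for other COS.
- **Analysis (section 2.2.4).** Uptake is summarised as the median percentage of each trial's outcomes that match the COS, and as the proportion of overlapping outcomes per disease. The text neither aligns registration periods between COS of different origin nor requires a trial to have been registered after the COS was published.

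**The concern.** The article announces a contrast by developer origin and then lets the sampling rule for trials depend on developer origin. Under the text, a Chinese-developed COS with fewer than 40 matching trials stays in with a longer window, while any other COS in the same position is left out. The two groups can then differ in the years from which their trials come and in how they were selected, as well as in who developed the COS.

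Two consequences follow when the exception is triggered. First, any general change over time in the choice of outcomes enters the contrast. Second, if the window is widened backwards, some added trials may have been registered before the COS was published. Their investigators could not have taken it up, so their overlap says nothing about uptake.

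A smaller flaw sits in the same sentence. A longer registration window can cure a shortfall of trials, but it cannot cure failure of the criterion on publication since 2012. The remedy is nevertheless attached to failure of the criteria as a whole.

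**Working it through.** **The plan's own figure.** Section 2.2.3 wants 20 responding trialists and expects 50% non-response. 20 / (1 − 0.5) = 40, so the floor of 40 trials reproduces exactly. Its only stated justification is survey yield; nothing ties it to the precision of the uptake comparison.

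**The rule by group.**

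| Situation | Chinese-developed COS | Other COS |
|---|---|---|
| At least 40 matching trials in 2021–2022, published since 2012 | Included, 2021–2022 | Included, 2021–2022 |
| Fewer than 40 matching trials | Included, window widened without stated limit | Not included |
| Published before 2012 | Window widened, which cannot cure the failure | Not included |

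The last row is probably rare for Chinese-developed COS, because the Background dates the introduction of the concept in China to 2013. In practice the trigger is the 40-trial floor.

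**Illustration of what widening does.** The document gives no number of matching trials per COS, no direction of widening and no time trend. The following inputs are therefore assumptions: a constant registration rate, backward widening until 40 trials are reached, and comparator COS kept on 2021–2022. Let k be the number of matching trials in 2021–2022.

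- Window length: W = 40 / (k / 2) years.
- Window start: 2023 − W.
- Shift of the window midpoint: (W − 2) / 2 years.
- Share of trials registered before a COS published at time p: (p − start) / W, not below 0.
- Gap due to time alone, for an assumed drift in overlap of 1 to 3 percentage points per year: drift × midpoint shift.

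| k | W (years) | Start | Midpoint shift (years) | Before a COS published at start of 2021 | Before a COS published at start of 2019 | Gap from drift (points) |
|---|---|---|---|---|---|---|
| 40 | 2 | 2021.0 | 0 | 0% | 0% | 0 |
| 30 | 2.7 | 2020.3 | 0.33 | 25% | 0% | 0.3–1.0 |
| 20 | 4 | 2019.0 | 1 | 50% | 0% | 1–3 |
| 10 | 8 | 2015.0 | 3 | 75% | 50% | 3–9 |

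For k = 20: W = 40 / 10 = 4; start = 2023 − 4 = 2019; shift = (4 − 2) / 2 = 1; share before the start of 2021 = (2021 − 2019) / 4 = 50%.

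If the window were widened forwards instead, no pre-publication trials would be added and the sign of the drift gap would reverse. Section 2.1.2 dates the start of the study to 7 April 2023, so there was little forward room at that point. That makes backward widening the likelier reading, but this is an inference.

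**A check on the fixed window.** Pre-publication trials are not unique to the exception. For a COS of any origin published at the start of 2022, (2022 − 2021) / 2 = 50% of trials in the 2021–2022 window precede it. A remedy on this point should therefore apply to all COS.

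**The case against.** The strongest reply is that the origin question is exploratory. It is not among the three aims in the Background, and no test or formal contrast is specified for it. The 40-trial floor exists to secure enough survey responses, so widening the window for a COS of special interest to Chinese trialists is a legitimate recruitment device. If each Chinese-developed COS reaches 40 trials in 2021–2022, nothing is distorted. All of this stands, and it limits the consequence to a descriptive contrast that is hard to interpret. It does not remove the asymmetry, because the same trials feed both the survey and the uptake comparison.

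A reader might infer four stronger criticisms that the document does not support:

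- **That Chinese origin is defined by journal language.** Section 2.1.3 makes a Chinese-language journal an additional route of entry. The question in 2.1.3 and the exception in 2.2.3 are both worded by developer, developer location is extracted, and a Chinese team publishing in English can still enter through the COMET search.
- **That uptake would be halved when half the trials precede the COS, for example from 20% to 10%.** This treats uptake as a rate that is zero before publication. Section 2.2.4 measures outcome overlap. A trial registered before the COS can share outcomes with it, and a median across trials does not simply halve.
- **That the focus of most Chinese COS on traditional Chinese medicine (TCM) is ignored.** Trials must match in scope, the intervention is extracted, and Table 2 grades overlap on an intervention axis. The text does not say that origin results will be split by TCM scope, but that is a reporting suggestion.
- **That the origin question cannot be answered at all.** The distortion is conditional on the exception being used.

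**Conclusion.** The point holds in a limited form. As written, section 2.2.3 ties developer origin to registration period whenever the exception is triggered, and it leaves the direction and extent of widening open. Backward widening can add trials registered before the COS existed. The document does not allow the size or direction of the resulting distortion to be derived. Under the stated assumptions the gap from time drift alone runs from 0.3 to 9 percentage points and the share of trials preceding a COS published at the start of 2021 from 25% to 75%; both are zero without expansion. These figures illustrate the mechanism and do not estimate the bias in this study. Separately, and with certainty, the remedy cannot repair failure of the publication-date criterion. What is affected is an exploratory descriptive contrast. The rule is nonetheless worth changing because the correction is specific and cheap.

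**What to change.** 1. Keep the widened window for survey recruitment if it is needed, and state its direction and limit.
2. Make the contrast by developer origin on a common registration window: either 2021–2022 for all COS, or the same widened window for the comparator COS in that disease.
3. In that contrast, count only trials registered after publication of the relevant COS, whatever its origin. COS publication time is already extracted, and the registration date is needed anyway to apply the 2021–2022 criterion.
4. Classify origin by the developer location already being extracted.
5. Reword the exception so that it refers to the 40-trial criterion only, and say what happens to a Chinese-developed COS published before 2012.
6. Optionally, show TCM and non-TCM scope separately as an aid to interpretation.

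The cost is a few sentences of protocol text and, if the comparator's window is widened too, some extra trial extraction. Some Chinese-developed COS will have fewer than 40 trials in the contrast, so their summaries will be less precise. The floor was set for survey yield, so falling below it in the contrast breaks no stated precision requirement.

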### Exploring uptake of COS in trialists in China

2.2

**
*2.2.1 Identification of clinical trials in the Chinese Clinical Trial Registry*
**

We will search the Chinese Clinical Trial Registry (
https://www.chictr.org.cn/historyversionpub.aspx) according to the disease name extracted for the published COS.

**
*2.2.2 Inclusion and exclusion criteria for clinical trials*
**

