Contact details of trialists (including applicant’s name, the registration contact person’s email and telephone number, the primary investigator’s name, the primary investigator’s email and telephone number) will be extracted, because they will be invited to participate in the online survey. The other data extracted will include: title, the primary investigator’s institutions, study type, disease name, population, intervention, outcomes, and outcome measurement instruments.

For comparing trial outcomes and COS, only published COS will be used. If there are more than two COS for a specific disease, the differences in scope between these COS will be discussed by two reviewers. 

We will compare the overlap in scope between clinical trials and COS according to the framework used in previous research.
^
9
^ The framework is shown in
Table 2.

**Table 2. T2:** The framework for assessing overlap in scope between clinical trials and COS.

		Intervention			
		COS is narrow	Exact match	COS is broader	Different intervention
Population	COS is narrow	A	B	C	D
	Exact match	E	F	G	H
	COS is broader	I	J	K	L
	Different subgroup of the population	M	N	O	P

We will calculate the median percentages of outcomes in each clinical trial that were specific matches, general matches, and non-matches with outcomes in each relevant COS. We will calculate the proportion of outcomes that overlap between the COS and clinical trials for each disease.

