**2.3.1.2 Data analysis**

Closed questions will be analyzed using descriptive statistics. Ratings for the barriers and facilitators to uptake will be summarized in terms of the median, range, and interquartile range. For open questions, thematic analysis will be used. All free text will be extracted in to a word document which RQ will read multiple times to organize the text into some initial themes and the author team will review the data and its assignment to the themes identified. The reason why the trialists used or did not use COS will be analyzed by content analysis. New suggested potential barriers and facilitators will be mapped to different themes.

**
*2.3.2 Semi-structured interviews*
**

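### The registry analysis measures agreement with the COS, but aim 2 and section 2.2 call it use or uptake, and no step joins it to survey-stated awareness

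*Protocol article*

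**What the plan says.** The second aim in the Background is to examine "the use of COS in clinical trials registered in the Chinese Clinical Trial Registry for these 25 diseases". Section 2.2 is headed "Exploring uptake of COS in trialists in China", and section 2.2.3 gives the comparison the same name: "A COS published since 2012 would be preferred to one published before 2012 for the analysis of COS uptake".

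Section 2.2.4 plans two statistics. The first is per trial: "We will calculate the median percentages of outcomes in each clinical trial that were specific matches, general matches, and non-matches". The second is per disease: "We will calculate the proportion of outcomes that overlap between the COS and clinical trials for each disease". Apart from contact details, the items taken from each trial are "title, the primary investigator’s institutions, study type, disease name, population, intervention, outcomes, and outcome measurement instruments". Whether the registry entry cites a COS is not among them.

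Trials must be registered in 2021 or 2022 (section 2.2.2). A COS must date from 2012 or later, with no upper date and no rule that it precede the trial (section 2.2.3).

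Section 2.3.1.1 gives each trialist one of three survey versions, according to whether the trial reports all, a few or none of the core outcomes. It examines knowledge and awareness, and sends the translated COS with the questionnaire. Section 2.3.1.2 adds: "The reason why the trialists used or did not use COS will be analyzed by content analysis". Section 2.3.2.2 describes interviewees' awareness and their decisions to look for and use a COS.

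**The concern.** Use of a COS means that it informed the choice of outcomes. Agreement means only that the same outcomes appear in both lists. Core outcomes are often ones that a trialist in the field would register anyway, so some agreement is expected with no use at all. The plan sets no background level against which to read the overlap.

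Two results are at stake. A disease could appear to have appreciable uptake when few of its trialists knew the COS. Differences between diseases could reflect how conventional their core outcomes are rather than how far the COS has spread.

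The plan gathers material that could help to separate the two, since survey version follows overlap category and awareness is asked. But no step reads the overlap result by the awareness answers. Sending the COS with the questionnaire may also prompt those answers.

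**Working it through.** **Inputs from the protocol article.** The plan wants 20 responses, expects 50% non-response and requires 40 trials per COS (section 2.2.3). Its figure reproduces: 20 / (1 − 0.5) = 40.

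**Assumed inputs.** The documents give neither the number of core outcomes *k* nor the probability *p* that a trialist registers a given core outcome by habit. I take *k* = 5, *p* from 0.3 to 0.8, independence between outcomes and no real use. Overlap is counted as the share of core outcomes found in a trial.

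**Agreement with zero use.** Mean share = *p*; at least one core outcome = 1 − (1 − *p*)^5; full set = *p*^5.

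| *p* | Mean share | At least one | Full set |
|---|---|---|---|
| 0.3 | 30% | 1 − 0.7^5 = 83.2% | 0.3^5 = 0.2% |
| 0.5 | 50% | 1 − 0.5^5 = 96.9% | 0.5^5 = 3.1% |
| 0.8 | 80% | 1 − 0.2^5 = 99.97% | 0.8^5 = 32.8% |

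Two diseases with habit rates of 0.3 and 0.8 would differ by 50 percentage points in mean overlap, with no use in either. The mean does not depend on independence. If outcomes tend to be registered together, the at-least-one figures fall and the full-set figures rise.

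**Other assumptions.** With *k* = 6 and *p* from 0.2 to 0.6, 74% to 99.6% of trials show at least one core outcome and 0.01% to 4.7% show the full set. With *k* = 4 the full set appears in 0.2% to 13%. Full-COS reporting is therefore much less affected, unless the COS is small and its outcomes are common.

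**What an observed overlap can mean.** Suppose users report 90% of the COS and non-users a share *b*. With a fraction *a* of users, overlap = 0.9*a* + (1 − *a*)*b*, so *a* = (overlap − *b*) / (0.9 − *b*). For an overlap of 45%:

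- *b* = 0: 0.45 / 0.90 = 50% users
- *b* = 0.20: 0.25 / 0.70 = 36%
- *b* = 0.40: 0.05 / 0.50 = 10%
- *b* = 0.45: 0 / 0.45 = 0%

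The same overlap fits anything from no users to half, depending on a quantity the plan does not estimate.

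**Dates.** With no upper limit on COS publication, a COS could be compared with a trial registered in 2021 before that COS appeared. Such agreement cannot come from the published COS.

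**What the survey can deliver.** With 20 of 40 responding, 5 aware respondents give 25% (95% Wilson interval 11% to 47%). If none or all of the 20 non-respondents were aware, the share over all 40 trials would be 5/40 = 12.5% or 25/40 = 62.5%.

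**The case against.** The plan never states that overlap is use. Section 2.2.4 says overlap, section 2.3.1.1 sorts trialists by what they report, and the Discussion speaks neutrally of comparing chosen outcomes with existing COS. The Background defines a COS as a minimum to be measured and reported, so a trial that measures all of it meets the standard whatever the motive. Agreement is thus a legitimate descriptive measure. All of this stands, but it supports calling the result concordance. It does not support the words use and uptake in the aim, the heading and section 2.2.3.

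A reader might infer that the plan ignores awareness, or that section 2.3.1.2 assigns use by overlap category. The documents support neither. Awareness and reasons for use are collected by survey and interview, and nothing says that the reasons analysis takes its users from the overlap categories. Each respondent's overlap category is known through the survey version, so only the joining step is unstated. Nor can one say that the questionnaire lacks an item on consulting the COS at design, because it is in extended data not shown.

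The habit rates are hypothetical, and the largest percentages concern any overlap, which the plan does not itself call uptake. That is fair, and full-set reporting is more robust. A low awareness result under aim 3 would also warn readers. It would not show which agreement under aim 2 came from use.

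**Conclusion.** The point holds as a mismatch between what is measured and what it is called. Aim 2 is worded as use, the statistics planned for it measure agreement, and no written step connects agreement with stated awareness. Under the assumed values, zero use is compatible with some overlap in 83% to nearly 100% of trials and with the full set in 0.2% to 33%. These figures rest on five independent core outcomes and habit rates of 30% to 80%, none of which the documents give. They show what is possible and do not forecast the result.

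It would go too far to say that the study is bound to report false uptake, or that it has no means of telling use from coincidence. The survey offers a partial means, for respondents only. The change is worth making because it alters what can be concluded under aim 2 at little cost.

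**What to change.** 1. Label the section 2.2.4 results concordance with the COS, and bring aim 2, the heading of section 2.2 and the wording of section 2.2.3 into line.
2. Obtain the answer on whether the COS was known and consulted at design before the COS is shown, using an existing questionnaire item if there is one.
3. Cross-tabulate concordance (full, partial, none) by that answer among respondents, and show non-response in each concordance category.
4. Do not count as use any concordance in trials registered before the COS was published. Report those trials separately as a background level where the window contains them. With registration in 2021 and 2022 they will often be absent: a COS published before 2021 has none unless the window is widened, which section 2.2.3 allows for a COS developed by Chinese researchers.
5. Keep trialists who were unaware of the COS in the reasons analysis, and report unawareness as its own reason for non-use. Aim 3 covers knowledge and barriers and would lose information if they were dropped.

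The cost is some wording, at most one survey item, a change in when the COS is sent, a date check and one table. The limits should be stated. Stated use is known only for respondents, about half by the plan's assumption, and is imprecise per COS. Where the registration applicant answers in place of the primary investigator, that person may not know how outcomes were chosen.
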